### Eligibility criteria

2.8

#### Diagnostic criteria for hyperuricemic nephropathy

2.8.1

According to the diagnosis, syndrome differentiation, and curative effect in patients with hyperuricemic nephropathy (trial Scheme) [10], a patient must fulfill the requirements of the third item, and at least one of the five other items listed below, in order to be diagnosed with hyperuricemic nephropathy.(1)The patient should be a middle-aged male or post-menopausal female who has often had gouty arthritis, gout nodulosis, or uric acid stones in the urinary trac.(2)The patient should demonstrate clinical manifestations of chronic interstitial glomerulonephritis, including mild to moderate proteinuria or decreased urinary concentrations (low osmotic pressure in the first-morning urine) in the early stage, and hypertension and azotemia in the later period.(3)Serum uric acid levels should be > 357 μmol/L for females and >417 μmol/L for males.(4)Urine sediment examination results should demonstrate uric acid crystallization, microscopic or gross hematuria, and pyuria.(5)Urine sediment examination results should demonstrate uric acid crystallization, microscopic or gross hematuria, and pyuria.(6)Renal histology is mainly manifested as renal tubule-interstitial lesions, and birefringent needle-like urate crystals are found in the renal interstitium and renal tubules.

#### Diagnostic criteria for patients with stages 3–4 of CKD

2.8.2

Recruited male and female patients should exhibit abnormal laboratory test results or anomalies of renal structure and a loss of endocrine function beyond three months. Patients should be diagnosed with an eGFR value ≥ 15 mL/min/1.73 m^2^ and <60 mL/min/1.73 m^2^. The eGFR should be computed utilizing the chronic kidney disease epidemiology collaboration (CKD-EPI) creatinine equation.

#### Diagnostic criteria for TCM syndrome differentiation

2.8.3

Based on an evaluation of the diagnosis, syndrome differentiation, and curative effect in patients with hyperuricemic nephropathy (trial Scheme) [10], a patient, to be diagnosed with the obstruction of phlegm turbidity and blood stasis syndrome, has to perform no less than three of the primary symptoms listed below.

Primary symptoms.◆Pain or swelling in the joints◆Joint stiffness and deformation, possibly with subcutaneous gout nodules◆Impaired flexion and extension of joints◆Fatigue and swelling limbs◆Sticky and greasy in the mouth◆Increased nocturia◆Frequent urination◆Waist sinking and pain◆A red or dark tongue with ecchymosis◆A yellow and greasy coating of the tongue◆A string-like and slippery pulse

Inclusion criteria and exclusion criteria are listed below (Table 1).

**Table 1 tbl1:** Eligibility criteria for the trial.

Inclusion criteria
To be eligible for participation patients must be:
◆ Individuals diagnosed with hyperuricemic nephropathy beyond three months as listed above, at the same time diagnosed with obstruction of phlegm turbidity and blood stasis syndrome in TCM
◆ Aged between 18 and 75 years
◆ The eGFR value ≥ 15 mL/min/1.73 m^2^ and <60 mL/min/1.73 m^2^
◆ Should be able to provide serum or urine pregnancy test results (for females), 24 h earlier than JNSF administration
◆ Should be able to provide the investigators with informed consent in written form for trial enrollment
**Exclusion criteria**
Patients are to be unentitled for participation if:
◆ The patient is probably or distinctly possible or definitely allergic to any of the components of the intervention or control drugs
◆ 24-h proteinuria value > 1 g
◆ The patient is diabetic
◆ The patient has had unresolved acute kidney injury, nephrotic syndrome, inherited kidney diseases, another serious disease, or renal transplantation in the previous 3 months
◆ The patient disagrees to engage in the study
◆ The patient has chronic hepatitis, or hepatic dysfunction induced by drug or other pathogens
◆ The patient has recently participated in another clinical trial
◆ The patient is taking medications as similar with JNSF
◆ The patient has a complication or history of malignant tumors, while made an exception for that the malignant tumor is untreated and not recurred within 5 years

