### Randomization procedures

2.6

Potential participants will be screened for eligibility a week anterior to study randomization. Participants will be randomly assigned as a consequence of a randomization schedule to receive JNSF treatment coupled with febuxostat (intervention group) or JNSF placebo treatment coupled with febuxostat (control group).

These treatments are changed into two groups A and B by the independent statistician. A random numbering (1:1) is formulated based on complete randomization with a block size of 4 via SPSS software.

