**Rejection criteria**
Patients will be eliminated if they correspond with one of the rejection criteria:
◆ Do not meet inclusion criteria or meet exclusion criteria
◆ Vacate from informed consent
◆ If no next-in-line statistics are acquired after admission
◆ Commit a serious violation of trial rules, including receiving other therapies concurrently to such an extent that efficacy and safety could be indistinguishable

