### Manufacture of study supplements

2.9

Patients will be randomized into either the JNSF or the control group and orally administered JNSF or placebo. Patients in the JNSF group will receive 10.2 g of the allocated intervention drug JNSF granules twice a day as oral administration, 30 min later than breakfast and dinner lasting 24 weeks. Respectively, the control group will accept 10.2 g of the placebo twice a day as oral administration. The appearance of the placebo is consistent with that of JNSF granules, in terms of packaging, appearance, particle shape, color and taste, but it contains one-tenth of the volume of drugs in the JNSF granules. The JNSF granules, as well as the placebo granules will be produced by Jiangyin Tianjiang Pharmaceutical Co., Ltd. (Wuxi City, Jiangsu Province, China), in accordance with certain manufacturing practices. The composition and function of each herb of JNSF have been outlined in Table 2.

**Table 2 tbl2:** Composition, effects and pharmaceutical action of the Chinese herbal medicines that constitute JNSF.

Ingredient	Granule dose	Effect (TCM)	Pharmaceutical action
Semen Vaccariae (wangbuliuxing)	10g	Promotes blood circulation and removes obstruction in collaterals	Attenuates human endothelial cell oxidative stress injury
		Promotes lactation for resolving carbuncle	Inhibits the growth and metastasis of malignant cells
Semen sinapis (baijiezi)	10g	Dissipates phlegm and expels retained fluid	Suppresses the mRNA expression of a panel of inflammatory mediators
		Resolves masses and removes edema	
Semen Plantaginis (cheqianzi)	15g	Reduces heat and induces diuresis	Reduces the content of urinary protein and UA and deregulates the expression of inflammatory mediators
		Eliminates dampness and frees strangury	
Rhizoma Dioscoreae hypoglaucae (fenbixie)	10g	Promotes diuresis and removes turbidity	Prevents oxidative stress and reduces levels of advanced glycosylation end products in the kidney
		Dispels pathogenic wind and dredges channel blockade	
Fructus crataegi (shanzha)	10g	Resolves food stagnation and invigorates the stomach	Improves lipid metabolism in the serum, liver, and adipose tissue
		Activates qi for resolving blood stasis	
Radix clematidis (weilingxian)	15g	Dispels pathogenic wind and eliminates dampness	Inhibits iNOS gene expression
		Removes obstruction in collaterals for relieving pain	
Radix et rhizoma rhei (dahuang)	10g	Removes heat and dredges the intestine	Anti-renal fibrosis

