		Cools the blood and removes toxicity	
		Eliminates blood stasis for dredging channels	Increases the level of serum HIF-1α

iNOS, inducible nitric oxide synthase; HIF-1α, hypoxia inducible factor-1.

Each group will be provided with diet instructions [11], behavioral guidance and health-related education [12]. In addition, they will receive febuxostat as a urate-lowering therapy. The dose of febuxostat should be 20 mg once a day after study initiation to week 4, and this should be increased to 40 mg once a day at week 5 if the target is not met, and maintained until week 24.

Based on KDIGO Clinical Practice Guideline for CKD, medical decisions will be arranged reasonably for patients in either group as basic treatment on how to treat hypertension [13], renal anemia [14], CKD-MBD [15], lipid management [16], concurrent infections, as well as other diseases, with the exception of the TCM herb decoction. The investigators will record the name and dosage of any administered medicine.

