## Discussion

3

Traditional Chinese medicine which can improve renal function and reduce uric acid levels is widely used for the treatment of hyperuricemia-associated diseases in China. According to TCM theory, the obstruction of phlegm turbidity and blood stasis syndrome majorly represent the pathogenesis of advanced hyperuricemic nephropathy. The dissipation of phlegm and removal of blood stasis are the main approaches for its treatment. As described previously, the main mechanism of action of JNSF is that it resolves phlegm, reduces turbidity, promotes blood circulation, and promotes collaterals, which is in accordance with the pattern observed for patients at advanced stages of hyperuricemic nephropathy. Moreover, as discussed in our previous study, we found that JNSF can lessen urate crystallization, suppress renal inflammation and improve renal function in a rat model of hyperuricemic nephropathy, and identified its mechanism of action. However, in TCM, syndrome differentiation is mostly derived from empirical medicine and there is a deficiency of convincing evidence. Consequently, we conduct a trial to enroll 118 patients with stages 3–4 CKD and hyperuricemic nephropathy.

Evidence-based medicine (EBM) forms the basis of this study, and each indicator used in the criteria could be quantified in modern medicine. To ensure the use of high-quality methodology and strictly adhere to quality control requirements, we have developed this protocol using the SPIRIT checklist [18]. The accomplishment of this trial might highlight evidence concerning the effectiveness and safeness of JNSF to treat stages 3–4 CKD patients with hyperuricemic nephropathy. We classify the patients into two groups: JNSF plus febuxostat versus JNSF placebo plus febuxostat. JNSF may not be as potent as febuxostat in lowering the uric acid levels, but is advantageous for improving the renal function, according to our clinical observations. Therefore, the primary outcome will be observed in terms of eGFR instead of a decline in uric acid levels. To evaluate the safety, with the exception of kidney function, several parameters will be measured and monitored before and after treatment, including the hepatic function, electrolyte levels, blood and stool routine, blood pressure, heart rate, and electrocardiogram-related differences.

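### The exclusion for JNSF-like medicines has no look-back, the on-trial herbal restriction names only decoction, and the elimination rule for breaches conflicts with the intention-to-treat analysis

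*Protocol article*

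**What the plan says.** **Entry.** One exclusion criterion in Table 1 of the protocol article (section 2.8.3) reads "The patient is taking medications as similar with JNSF". It names no dosage form and gives no period before entry. Another criterion in the same list does carry a window: "renal transplantation in the previous 3 months". On timing, section 2.6 says "Potential participants will be screened for eligibility a week anterior to study randomization". Table 3 shows one screening visit (V0, week -1) and no washout or run-in.

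**During treatment.** Section 2.9 allows guideline-based background treatment in both groups "with the exception of the TCM herb decoction". It adds: "The investigators will record the name and dosage of any administered medicine". The study product is given as "10.2 g of the allocated intervention drug JNSF granules twice a day".

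**Breaches.** The rejection criteria in Table 1 eliminate patients who meet an exclusion criterion. They also eliminate those who seriously violate trial rules, including by "receiving other therapies concurrently to such an extent that efficacy and safety could be indistinguishable".

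**Analysis.** Section 2.15 places every enrolled patient in the primary analysis under the intention-to-treat principle and handles missing data by multiple imputation.

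**Setting.** The single site is a hospital affiliated to a university of traditional Chinese medicine (TCM). The Discussion says TCM is in wide use in China for hyperuricemia-associated disease. It describes JNSF as less potent than febuxostat on urate, "but is advantageous for improving the renal function, according to our clinical observations".

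**The concern.** The trial estimates what JNSF adds to febuxostat. That contrast is clean only if control patients do not receive the same herbs by another route. The entry criterion and the on-trial restriction ought to describe the same set of products, and they do not. The first covers any similar medicine in any form. The second names decoction, a form that the study product does not take.

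The entry criterion also leaves a gap in time. A patient who took JNSF or something similar for months and stopped just before V0 does not meet it. The site and the Discussion make earlier exposure plausible, but no rate is given.

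Two things are at stake. Herbal use in the control arm pulls the estimated effect towards zero. And if such patients are removed after randomisation, the primary analysis no longer contains everyone randomised, contrary to section 2.15.

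**Working it through.** **1. The texts side by side**

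| Place | Products covered | Time covered | Consequence |
|---|---|---|---|
| Table 1, exclusion | JNSF-like, any form | Present use only | Not enrolled |
| Section 2.9 | TCM decoction | Treatment period | None stated there |
| Table 1, rejection | Anyone meeting an exclusion; confounding co-therapy | After entry | Elimination |
| Section 2.15 | – | – | All enrolled patients analysed |

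Rows 1 and 2 differ in scope. Rows 3 and 4 conflict about what happens to the data of a patient who takes a JNSF-like product on trial.

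**2. The plan's own sample size (section 2.5)**

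Inputs: difference 10, SD 18.1 mL/min/1.73 m², type 1 error 5% (taken as two-sided), power 80%, drop-out 10%.

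- Normal approximation: n = 2 × (1.960 + 0.842)² × 18.1² / 10² = 2 × 7.849 × 327.61 / 100 = 51.4, so 52 per group.
- Noncentral t: power is 0.797 at 52 and 0.804 at 53, so 53 per group. This matches the plan.
- Drop-out: 53 / 0.9 = 58.9, so 59 per group and 118 in total. This also matches.

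**3. Concurrent use in the control arm (illustration)**

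Suppose a fraction q of control patients take a JNSF-like product and gain a share s of its effect. The contrast becomes 10 × (1 − q × s). The documents give neither q nor s, so the loss q × s is assumed. SD is held at 18.1. Power uses the noncentral t distribution with noncentrality d / (18.1 × √(2/n)). Required n is the normal approximation; the exact t calculation adds about one patient, as in step 2.

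| Assumed loss | Contrast d | Power at 53 | n per group for 80% | With 10% drop-out |
|---|---|---|---|---|
| 0% | 10.0 | 0.804 | 52 | 58 |
| 5% | 9.5 | 0.763 | 57 | 64 |
| 10% | 9.0 | 0.718 | 64 | 72 |
| 20% | 8.0 | 0.616 | 81 | 90 |
| 30% | 7.0 | 0.505 | 105 | 117 |

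If all 59 per group gave data, the same formula gives noncentrality 10 / (18.1 × √(2/59)) = 3.00 and power 0.845. With a 5% loss it is 0.807, and with a 20% loss 0.663. The reserve is then slightly larger, but still small.

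These rows count control-arm use only. Equal extra use in the JNSF arm, with an additive effect, would offset the loss.

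**4. Prior use**

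Take a prior user who enters with the full 10-unit benefit.

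- If the effect fades on stopping, the change to week 24 is about 0 on JNSF and about −10 on placebo. The between-arm difference is still 10.
- If placebo patients keep a fraction r of the benefit to week 24, the difference in prior users is 10 × (1 − r). With a fraction p of prior users, the trial-wide difference is 10 × (1 − p × r).

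Attenuation therefore needs the benefit to persist for 24 weeks after stopping. The documents give neither p nor r and say nothing on persistence, so no size can be put on it.

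**The case against.** **Decoction is not the only bar.** The exclusion criterion covers any dosage form. The first rejection rule removes patients who meet an exclusion criterion, and the second reaches confounding co-therapy. Read together, they may well catch a control patient who starts JNSF-like granules. This stands: a reader might infer from section 2.9 that every other herbal form is permitted, and the documents do not support that. What remains is that the one explicit on-trial restriction has a narrower scope than the exclusion, and that the wider rules act only afterwards, by elimination.

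**Use is already recorded.** Medical history is taken at V0, and concomitant drugs are recorded at V0 to V4. True, but recording reveals contamination without preventing it.

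**The article is condensed.** A washout length may stand in the full protocol. That is a fair reason not to criticise a missing number of weeks. The criterion as printed, however, is a stated rule limited to present use, and its meaning changes if a look-back applies.

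**Prior use is balanced.** It precedes 1:1 randomisation, so it should fall on both arms alike. This stands. A reader might infer that recent users bias the comparison or shrink it by a known amount. Step 4 shows that this needs persistence, on which the documents are silent; if placebo simply means withdrawal, the contrast is unchanged.

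**Other harms are speculative.** A reader might also infer weakened blinding or flattered safety from experienced users. Nothing in the documents shows that such patients will enrol, and the placebo is described as matched in taste. These arguments are not relied on here.

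**Conclusion.** The point holds in a limited form. The entry criterion leaves very recent users eligible. The explicit on-trial restriction is narrower than that criterion and names a form that the study product does not have. Elimination after randomisation conflicts with the intention-to-treat statement.

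The more direct threat is concurrent use in the control arm. If JNSF works, such use biases towards no difference; it does not create a false positive. At 53 evaluable patients per group the design has power 0.804, so each of the assumed losses in the table takes it below 80%: 0.763 at 5%, 0.616 at 20%. These figures illustrate how little slack there is and do not estimate contamination. They rest on the plan's own difference and SD, on a two-sided test and on assumed losses in the control arm alone.

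For prior use the conclusion is weaker: added noise or attenuation is possible, carry-over is not demonstrated, and its amount cannot be derived from the documents. None of this invalidates the trial. It is worth correcting because the change is small and the data cannot be repaired afterwards.

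**What to change.** Reconcile four places: the exclusion and rejection criteria in Table 1, the background-treatment sentence in section 2.9, and the analysis population in section 2.15.

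- Word the on-trial restriction so that it covers JNSF-like herbal products in the same scope as the exclusion, whatever the dosage form.
- State that patients who breach it stay in the intention-to-treat analysis. If the sponsor wants an analysis without them, name it as supplementary.
- State a look-back for prior JNSF-like use. The investigators should set and justify its length. The 3-month window elsewhere in Table 1 concerns kidney and other serious disease and transplantation, and gives no basis for herbal carry-over.
- Use the medical history and concomitant-drug data already collected at V0 to record prior herbal use, so that its frequency can be reported by arm.

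The cost is an amendment to a few sentences, with no new visits or measurements. The downside is possibly slower recruitment at this TCM hospital, since some patients may have to wait or be ineligible.

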**Rejection criteria**
Patients will be eliminated if they correspond with one of the rejection criteria:
◆ Do not meet inclusion criteria or meet exclusion criteria
◆ Vacate from informed consent
◆ If no next-in-line statistics are acquired after admission
◆ Commit a serious violation of trial rules, including receiving other therapies concurrently to such an extent that efficacy and safety could be indistinguishable

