**Drop-out and Termination criteria**
Patients are to be terminated on condition that they correspond with one of the following criteria:
◆ The participant withdraws from the trial (because the patient becomes invalid, lost, or dies accidently)
◆ The interviewee is terminated during the trial (for reasons such as poor compliance, withdrawal of informed consent, prohibition of drug use, or safety-related problems)
◆ When SAEs or other diseases occur, it is not appropriate to continue to conduct
◆ Incomplete data affects the evaluation of efficacy and safety
◆ A serious violation of trial procedures has occurred
◆A hepatocellular injury is detected because of the abnormally elevated liver enzymes: level of alanine transaminase (ALT) or aspartate transaminase (AST) is more than three times of the upper limit of normal (ULN)

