### Statistical analysis

2.15

The independent statisticians will formulate a formal and detailed plan for statistical analysis prior to locking the database. Comparing the baseline demographic data of each group will use with a χ^2^ test or Student's t-test. The means ± standard deviations or medians will express continuous variables, and an independent *t*-test or the Wilcoxon rank sum test will be used to analyze differences of such variables. Repeated measures ANOVA will be built for these outcomes. The numbers and percentages will express categorical variables, and the Fisher exact test or the Mann-Whitney *U* test will be used to calculate and compare differences in such variables respectively. The missing data will be handled with multiple imputation. According to the intention-to-treat principle, all patients enrolled will be embraced in the primary analysis. An independent statistician will use SPSS 24.0 to perform the statistical analysis. Calculations will be performed using GraphPad Prism 6.01 software.

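### The rejection criteria, read naturally, remove randomised patients whom the intention-to-treat primary analysis is meant to keep

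*Protocol article*

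**What the plan says.** Table 1 of the protocol article (section 2.8.3) contains two separate lists that act on patients already in the trial.

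- **Rejection criteria.** The rule is "Patients will be eliminated if they correspond with one of the rejection criteria". The grounds are "Do not meet inclusion criteria or meet exclusion criteria"; withdrawal of consent; "If no next-in-line statistics are acquired after admission"; and "Commit a serious violation of trial rules, including receiving other therapies concurrently to such an extent that efficacy and safety could be indistinguishable".
- **The list of drop-out and termination criteria.** The rule is "Patients are to be terminated on condition that they correspond with one of the following criteria". The grounds include withdrawal, loss or death, termination "for reasons such as poor compliance, withdrawal of informed consent, prohibition of drug use, or safety-related problems", SAEs, a serious violation, raised liver enzymes, and "Incomplete data affects the evaluation of efficacy and safety".

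Section 2.15 (Statistical analysis) defines the primary population: "According to the intention-to-treat principle, all patients enrolled will be embraced in the primary analysis". It assigns missing data to multiple imputation and names no exception. The caption of Fig. 1 also refers to the intention-to-treat analysis. The article names no per-protocol or other secondary set.

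**The concern.** Intention-to-treat protects the comparison because membership of each arm is fixed by randomisation and nothing that happens later changes it. A rule that removes patients for lacking later data, for taking other therapy or for violating the protocol gives up that protection. Such events can depend on how the patient is doing and on which treatment the patient is taking.

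Two of the grounds also collide with the missing-data plan. A patient with no data after entry, or with incomplete data, is the case imputation is there to handle. If that patient is removed first, there is nothing left to impute. Whether a violation is serious, or other therapy has gone too far, is a matter of judgement, so the rule leaves room for discretion over who is compared on the primary outcome.

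**Working it through.** **1. Does *eliminated* mean removed from the data?** The text does not say from what. Three features point to the data set:

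- Stopping participation has its own list under a different verb (*terminated*). Withdrawn consent and serious violation stand in both lists, which would be redundant if the verbs meant the same.
- A patient with no data after admission leaves little to stop, so that ground works mainly as an analysis exclusion.
- The violation ground is justified by efficacy and safety no longer being distinguishable. That is a test of evaluability, not of patient care.

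**2. Each ground against section 2.15.**

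| Ground | List | Conflict with analysing all enrolled patients? |
|---|---|---|
| No later data | Rejection | Yes, if *eliminated* means from the data |
| Serious violation or concurrent therapy | Rejection | Yes, same condition |
| Withdrawn consent | Rejection (and termination) | Yes, same condition |
| Eligibility failure | Rejection | Only if found after randomisation; timing not stated |
| Incomplete data | Termination | Reads as an exclusion, against imputation |
| Compliance, safety, SAEs, liver enzymes | Termination | No; these patients can stay in the analysis |

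**3. The plan's own figures (section 2.5).** Inputs: difference 10, SD 18.1, type I error 5%, power 80%, drop-out 10%. A two-sided two-sample t-test needs 52.4, so 53 per group. Then 53 / (1 − 0.10) = 58.9, so 59 per group and 118 in total. The stated sample size reproduces, and this point does not change it.

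**4. Size of a possible bias (assumed scenario).** Suppose there is no true effect. A fraction f is removed from one arm only, and the removed patients average D lower eGFR than those retained. The full-arm mean is then (1 − f) × m + f × (m − D) = m − f × D, where m is the retained mean. Removal therefore shifts the contrast by f × D.

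- f = 0.10, D = 10: 0.10 × 10 = 1.0 mL/min/1.73 m²
- f = 0.10, D = 18.1: 0.10 × 18.1 = 1.81 mL/min/1.73 m²
- Against the planned effect: 1.0 / 10 = 10% and 1.81 / 10 = 18%

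For the type I error at f = 0.10, the standard error with 59 × 0.90 = 53.1 and 59 patients is 18.1 × √(1/53.1 + 1/59) = 3.42. The two-sided error is 1 − Φ(1.96 − b/3.42) + Φ(−1.96 − b/3.42), where b is the shift. The range is:

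| f | D = 5 | D = 10 | D = 18.1 |
|---|---|---|---|
| 10% | shift 0.5, error 5.2% | 1.0, 6.0% | 1.8, 8.3% |
| 20% | 1.0, 5.9% | 2.0, 8.7% | 3.6, 17.6% |

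(The 20% row uses 47.2 and 59 patients.) Only the SD of 18.1, the 59 per group and the 5% level come from the article. Its 10% is a drop-out allowance for both groups; using it as a one-arm removal rate is an assumption, as are 20% and the values of D. If both arms lose similar patients in similar numbers, the shifts largely cancel.

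**The case against.** The best defence is that the conflict is inferred. The rejection criteria sit in an eligibility table and never mention an analysis set. The only section that defines the analysis population is clear, and it promises a detailed statistical plan before database lock. That plan may use the rejection criteria to define a per-protocol set, and an article need not repeat it. This stands in part: removal from the primary analysis is the natural reading, not an explicit statement. It does not dispose of the point, because the article makes two statements about the same patients and a later plan would have to override one of them.

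A reader might infer more than the text supports:

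- **That the whole termination list breaks intention-to-treat.** It does not. Apart from incomplete data, it concerns stopping participation, and a terminated patient can remain in the analysis through imputation. SAEs and poor compliance appear only in that list, not among the rejection criteria.
- **That termination ends collection of week-12 and week-24 eGFR.** The article does not say so. If collection did stop, missingness could be informative, which is a separate risk.
- **That imputation would treat those who leave as if they were completers.** The imputation model is not given, and it could condition on eGFR already observed.
- **That every rejection ground arises after randomisation.** Eligibility failures may be found at screening.
- **That the bias favours JNSF.** Violations and added therapy could occur in either arm, so the direction is not established.

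**Conclusion.** The point holds as a conflict between the rejection criteria, together with the incomplete-data item of the termination list, and the primary analysis population in section 2.15. It rests on reading *eliminated* as removal from the data set, which the wording favours but does not state. If the rule is applied that way, the eGFR comparison is no longer between the randomised arms. The size cannot be known from the article: 1.0 to 1.8 mL/min/1.73 m² illustrates a 10% loss confined to one arm, and few or balanced removals would give little bias. The remaining termination grounds do not contradict intention-to-treat. They matter only if outcome collection stops with participation, on which the article is silent. Because this settles who is in the primary comparison, it should be resolved before database lock.

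**What to change.** Four changes reconcile Table 1 with section 2.15:

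1. State that neither elimination nor termination removes a randomised patient from the primary analysis, and that patients are analysed in their assigned arm.
2. State that the rejection criteria define only a secondary per-protocol set.
3. Delete incomplete data as a ground for removal; imputation already covers it.
4. Separate stopping study drug from leaving the study. After drug stops, continue the creatinine/eGFR measurements already scheduled in Table 3, unless the patient withdraws consent to follow-up.

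The clinical stopping rules stay as they are. The cost is protocol and analysis-plan wording plus a few already scheduled blood tests in patients off drug. The small downside is that some off-treatment values may dilute the estimated effect.
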